### Statistical Analysis

No previous studies have investigated the effect of BiV pacing on the duration of level 3 care after cardiac surgery; previous studies have reported the total duration of CITU stay.

Pokushalov et al [20] reported an average CITU stay of 3.9 ± 0.6 days in the subjects after cardiac surgery, compared with 2.5 ± 0.5 days in subjects who had BiV pacing after cardiac surgery - a 36% reduction. We anticipate that the duration of level 3 care will be shorter than the duration of CITU stay, perhaps with less variance, but we have used these mean values and standard deviations for our power calculation.

Using the standard formula described by Campbell and Matchin [23]:

$$\text{Sample}\;\text{size}=\frac{2\times {\left({\text{Z}}_{1\alpha }+{\text{Z}}_{2\beta }\right)}^{2}\times \sigma^{2}}{\delta^{2}}$$

σ = standard deviation of the population

δ = anticipated benefit from the intervention

(Z_1α _+ Z_2β_) = normal distribution of function

(1-β) = 80% and α = 5%.

From standard tables (Z_1α _+ Z_2β_) ^2 ^= 7.85

$$\text{Sample}\;\text{size}=\frac{2\times \left(7.85\right)\times 0.6^{2}}{{\left(0.15\times 3.9\right)}^{2}}=\frac{5.652}{0.342}=16.5$$

In order to demonstrate a 15% reduction in the duration of level 3 care, with power 80% and with p < 0.05 for a two-sided test, the estimated total sample size required is 34 subjects.

For haemodynamic comparison of paired data at 18 hours to compare BiV pacing to standard (AAI) pacing, Hanke et al [24] observed a cardiac index of 2.7 ± 0.6 L/min/ml^2 ^in the standard pacing group. Allowing a 0.3 L/min/ml^2 ^(11%) improvement in cardiac index with BiV pacing, significance 5% and power 80%, a sample size of 32 subjects would be required.

Considering both of these previous studies, the minimum number of subjects who will be recruited and randomised into this study, will be 34; allowing for a 1/3 drop-out rate, the minimum number to be recruited will be 45. In the 2 cardiac surgical centres in which this study will be performed the proportions of all patients undergoing cardiac surgery who have impaired LV function and sinus rhythm, and who would therefore be eligible for the study are 2% and 8% (approximately 65 patients in a total of 1414 operations per year); this study should therefore be feasible within a maximum of 2 years.

Data obtained for the primary endpoint and haemodynamic studies will be analysed for normality using the Kolmogorov-Smirnov test. Normally distributed variables will be analysed using unpaired or paired Student's T tests respectively. Non-parametric data will be analysed using the Mann-Whitney U or Kruskal-Wallis test. If continuous variables are not matched between intervention and control groups at baseline, inter-group comparisons will be made using an analysis of covariance with adjustments made for baseline differences. Changes in proportions for categorical data will be analysed with the Chi-square test or Fisher's exact test.

Analysis will be intention-to-treat and a p-value of < 0.05 will be considered statistically significant.

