### Pre-operation

Patients will be invited to participate in the trial if they are awaiting cardiac surgery. This includes elective patients and in-house referrals scheduled for revascularisation, valve surgery or both. Subjects with a recent history of an acute coronary syndrome or episode of decompensated heart failure (< 30 days) will be included. However, unstable subjects with medically refractory angina and/or pulmonary oedema requiring emergency surgery will be excluded from the trial.

After enrolment an ECG will be performed to confirm sinus rhythm and measure QRS duration and a transthoracic echocardiogram to measure ejection fraction using the Simpson's bi-plane method of discs. A detailed echo study will be performed (GE, Vivid 7, Horten, Norway), to evaluate LV systolic and diastolic function, valve function and cardiac dyssynchrony- Table 5. Subjects with EF > 35% will exit the trial.

**Table 5 T5:** Echo protocol.

Echo window	Modality	Measurement
Parasternal long axis	MMode	LV internal dimensions
		LV wall thickness
		Septum to lateral wall delay
	Colour flow	Mitral regurgitation

Parasternal short axis	PW doppler	RVOT- pulmonary pre-ejection interval (PPEI)
	CW doppler	PA acceleration time

Apical 4 chamber	2D	LA and RA area
		LVEDV and LVESV
	MMode	Long axis displacement- RV lateral/LV septal and
		lateral walls
	Colour flow	Mitral regurgitation
	PW doppler	Mitral inflow
		LVOT- aortic pre-ejection interval (APEI)
		IVRT
	MVI	Medial and lateral E'
		Basal segments- peak velocity.

Apical 2 chamber	2D	LVEDV and LVESV
	MVI	Basal segments- peak velocity.

Apical 3 chamber	MVI	Basal segments- peak velocity.

Echo measurements of dyssynchrony included:

• Interventricular mechanical delay (= APEI-PPEI)

• Atrio-ventricular delay (APEI)

• Time-delay to peak systolic velocity in the basal segments of the septal and lateral wall using myocardial velocity imaging (MVI) Q analysis.

A repeat transthoracic echo will be performed after discharge from the cardiac intensive care unit (CITU) between day 3 and 5 post surgery.

Baseline blood tests will be sent to measure:

• Full blood count (Haemoglobin, haematocrit and mean cell volume)

• Creatinine (eGFR calculation)

• TnT: Troponin T

• BNP: Brain naturetic peptide

• NGAL: Neutrophil gelatinase associated lipocalin- renal injury

Blood samples will be taken at baseline, 18 hours, 48 hours and 72 hours after admission to CITU.

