### Randomisation

Randomisation into 2 groups will be performed after induction of anaesthesia using commercially available software to minimise for confounding variables -Table 6. Group 1 will be assigned to BiV pacing and group 2 to standard pacing. Standard pacing will be atrial inhibited pacing (AAI) unless right ventricular pacing is required, then atrial-synchronous right ventricular pacing (DDD-RV) is indicated. The intended duration of pacing will be 48 hours, but could be modified by the attending physician.

**Table 6 T6:** Variables considered at the time of randomisation.

Parameter	Reference	
LV size	≤ 60 mm	> 60 mm

QRS duration	≤ 120 msec	> 120 msec

Euroscore	≤ 10	> 10

Intra-aortic balloon pump	No	Yes

Valve surgery	No	Yes

Ejection fraction	≤ 20%	> 20%

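### Recruiting 45 patients does not cover a one-third drop-out: 30 would remain, fewer than the 34 and 32 the protocol requires; 51 are needed.

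*Protocol article*

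**What the plan says.** All the figures are in the Statistical Analysis section of the protocol article. For the primary endpoint, duration of level 3 care, it borrows the mean and standard deviation of intensive-care stay from an earlier trial, which "reported an average CITU stay of 3.9 ± 0.6 days in the subjects after cardiac surgery". It targets a 15% reduction, "with power 80% and with p < 0.05 for a two-sided test", and concludes that "the estimated total sample size required is 34 subjects". For the paired comparison of cardiac index at 18 hours it requires 32 patients.

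It takes the larger figure, 34, as the minimum to be entered and allocated, and then adds the drop-out allowance: "allowing for a 1/3 drop-out rate, the minimum number to be recruited will be 45". No other drop-out rate or inflation formula appears.

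Two other sections bear on when patients may be lost. Under Pre-operation, the echocardiogram follows enrolment and "Subjects with EF > 35% will exit the trial". Under Randomisation, "Randomisation into 2 groups will be performed after induction of anaesthesia". Some loss between recruitment and randomisation is therefore built into the design.

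**The concern.** A drop-out rate is a share of the patients who enter. To finish with a given number, that number must be divided by the proportion retained. The figure of 45 looks instead like the required number with one-third of itself added, which is always too small.

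The consequence is that a trial meeting its stated recruitment minimum, with exactly its stated drop-out, would finish below the size it says it needs for the primary endpoint and also for the main haemodynamic comparison. The 80% power claimed for each would not be reached. The base size has little slack to absorb this, because 16.5 per arm is only rounded up to 17.

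**Working it through.** **Inputs** (protocol article, Statistical Analysis)
- Primary endpoint: control mean 3.9 days, SD 0.6 days, reduction 15%, so the difference is 0.15 × 3.9 = 0.585 days. Two-sided 5% level, 80% power, squared sum of normal deviates 7.85.
- Paired cardiac index: difference 0.3, SD 0.6, 5% level, 80% power.
- Drop-out one-third; stated recruitment minimum 45.
- Assumptions: equal allocation, implied by the formula used and by 2 × 17 = 34; and 0.6 as the SD of the paired difference, the reading that reproduces the protocol's 32.

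**Step 1: reproduce the base sizes**
- Primary: 2 × 7.85 × 0.6² / 0.585² = 5.652 / 0.342 = 16.5, rounded up to 17 per arm, 34 in total. Agrees with the protocol.
- Paired: 7.85 × (0.6 / 0.3)² = 31.4, rounded up to 32. Agrees with the protocol.

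The error is therefore confined to the drop-out step.

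**Step 2: the drop-out allowance**
- Correct inflation: N / (1 − d) = 34 / (1 − 1/3) = 51. For the paired requirement alone: 32 / (2/3) = 48.
- How 45 arises: 34 × (1 + 1/3) = 45.3, rounded down.
- What 45 leaves after a one-third loss: 45 × 2/3 = 30, which is 4 short of 34 and 2 short of 32.
- What 45 does cover: 1 − 34/45 = 11/45 = 24.4%. At 25% it already falls short, since 45 × 0.75 = 33.75.

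**Step 3: power with 30 evaluable patients**

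The normal approximation is the basis of the protocol's own calculation. The t test is the analysis it plans for normally distributed data.

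Primary, normal approximation: power = Φ(0.585 / (0.6 × √(2/n)) − 1.96), with n per arm.
- n = 15: Φ(2.670 − 1.96) = Φ(0.710) = 76.1%
- n = 17: Φ(2.843 − 1.96) = Φ(0.883) = 81.1%

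Paired, normal approximation: power = Φ((0.3 / 0.6) × √n − 1.96).
- n = 30: Φ(2.739 − 1.96) = Φ(0.779) = 78.2%
- n = 32: Φ(2.828 − 1.96) = Φ(0.868) = 80.7%

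The t-test figures below come from the noncentral t distribution.

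| Comparison | Evaluable | Normal approximation | t test |
|---|---|---|---|
| Primary | 34 (required) | 81.1% | 78.7% |
| Primary | 30 (45 less one-third) | 76.1% | 73.2% |
| Paired cardiac index | 32 (required) | 80.7% | 78.2% |
| Paired cardiac index | 30 (45 less one-third) | 78.2% | 75.4% |

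Like for like, the slip costs about 5 points of power for the primary endpoint and 2.5 to 3 points for the paired comparison. The remaining gap between the t-test figures and 80% comes from using the normal formula in a small sample, not from drop-out.

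**The case against.** The arithmetic is not in dispute; the objections concern how much it matters.

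- **Both numbers are minimums.** The protocol also sets a floor of 34 randomised. If the losses fall before randomisation, 45 recruits give 30 randomised, that floor is unmet and recruitment would have to continue. This stands as a safeguard, but it does not rescue 45: it means that 45 is not the number that delivers 34.
- **Later drop-outs may still be analysed.** The analysis is by intention to treat, and the primary endpoint ends at the final step down from level 3 care before discharge from intensive care. A patient who stops the assigned pacing can still contribute it. This also stands: for losses after randomisation, 15 per arm is a worst case for the primary endpoint. It helps less with the paired comparison, because a missing 18-hour cardiac index is not recovered by intention to treat. Nor does it help with patients who were never randomised.
- **One-third might mean one-third of 34.** That is about 11 patients, or roughly a quarter of 45. It is not the ordinary meaning of a drop-out rate, and even then 45.3 should round up to 46 for a minimum.
- **The loss of power is small.** It is, at about 5 points or less. That bears on the consequence, not on whether the printed number is right.

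**Conclusion.** The concern holds. The recruitment minimum of 45 is inconsistent with the drop-out rate printed beside it. A one-third loss from 45 leaves 30 whether it occurs before or after randomisation, and 30 is below both required sizes. The number that matches one-third is 51; the loss that matches 45 is 24.4%.

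If all 30, and only those, are evaluable, primary power is 76.1% on the protocol's own basis or 73.2% by t test, and paired power is 78.2% or 75.4%. All four are below the stated 80%. These figures rest on the protocol's differences and SDs, equal allocation, and no outcome data from patients counted as drop-outs. If some of those patients contribute the primary endpoint, the loss of power is smaller. The mismatch between 45, one-third and 34 depends on none of these assumptions.

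**What to change.** Correct the sentence in the Statistical Analysis section in one of two ways.

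1. **Keep one-third and raise the number.** Give 51 as the minimum to recruit, and keep 34 randomised, analysed by intention to treat, as the target that decides when recruitment can stop.
2. **Keep 45 and correct the rate.** State that 45 allows for about 24% loss. Add that at one-third loss 30 would remain, with primary power of about 76% by the formula used in the protocol (about 73% by t test). Naming the method avoids setting a t-test figure against an 80% derived from the normal approximation.

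In either case, say which losses the allowance covers: exits between enrolment and randomisation, such as an ejection fraction found to be above 35%, or losses afterwards.

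The second option costs one sentence. The first adds 51 − 45 = 6 enrolments. The protocol estimates about 65 eligible patients a year and at most 2 years, so about 65 × 2 = 130 in all; 51 is 39% of these, against 35% for 45. The share of eligible patients who will take part is not given, so feasibility is plausible but not shown. The Trial status section reports 31 recruited; if these count towards the recruitment minimum, 20 more are needed to reach 51, against 14 to reach 45.

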### Haemodynamic studies

Haemodynamic studies will be performed after admission to the CITU after surgery (time = 0). The first study will be performed using a pulmonary arterial (PA) catheter, once the subject is euvolaemic and has a stable inotropic requirement. Cardiac output/index, pulmonary artery pressures, pulmonary capillary wedge pressure, central venous pressure, mean arterial pressure (MAP) and LV stroke work index will be recorded.

For thermodilution measurements, 3-5 sets of cardiac output measurements will be obtained to ensure consistent results. Measurements will be taken in the following pacing modes: atrial inhibited (AAI), right ventricle only (VVI), dual chamber (DDD-RV) and (DDD-LV) and BiV pacing. A minimum of 5 minutes will be allowed between changing the pacing mode and obtaining haemodynamic data. A pacing mode will be discontinued if it causes > 10 mm Hg drop in MAP. The base rate of pacing will be set at 10 beats above intrinsic rhythm up to a maximum heart rate of 110 bpm. The pacing modes will be selected at random. The studies will be repeated at 6 hours, 18 hours and 24 hours. After the 24 hour measurements the PA catheter will be removed. Cardiac output data will be also obtained from the radial pulse contour analysis (FLOTRAC) monitor at the same time points as the PA catheter, except for subjects with an intra-aortic balloon pump.

Optimisation of the atrio-ventricular (AV) and interventricular (VV) delays will be performed at 18 hours. A range of AV delays from 80-180 msec in 20 msec intervals and then VV delays from -40 to 40 msec (-ve indicating LV pre-activation) in 20 msec intervals will be performed. The optimal AV and VV delays will be programmed for patients assigned to BiV pacing.

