### Endpoints

The primary endpoint of the trial is the duration of level 3 care [22] required after cardiac surgery. Level 3 care is defined as the duration of invasive mechanical ventilation or multiple organ support or multiple inotropes/single inotrope and intra-aortic balloon pump. The majority of patients would reach the primary endpoint after extubation and then once weaned down to a single inotrope. In the cases where inotropes are restarted, the endpoint is taken to be the final transition from level 3 to level 2 care before discharge from the intensive care unit.

Secondary endpoints are:

• Cardiac index at 18 hours (AAI v BiV).

• Duration and total dose of inotropes/intra aortic balloon counter-pulsation.

• Renal function and requirement for haemofiltration.

• Arrhythmia after surgery until hospital discharge.

• Change in brain naturetic peptide, troponin T and neutrophil gelatinase associated lipocalin.

• Myocardial infarction, re-intubation or re-sternotomy.

• 30 day all cause mortality.

Subjects will complete the trial 30 days after the operation.

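### For non-normal data the plan names only independent-sample rank tests, although the haemodynamic comparison is within-patient and was sized as paired

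*Protocol article*

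**What the plan says.** All references are to the protocol article.

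- **Design of the measurements (Haemodynamic studies).** Every patient is studied in five modes: "Measurements will be taken in the following pacing modes: atrial inhibited (AAI), right ventricle only (VVI), dual chamber (DDD-RV) and (DDD-LV) and BiV pacing". After the first study on the intensive care unit, "The studies will be repeated at 6 hours, 18 hours and 24 hours".
- **Endpoint (Endpoints).** The first secondary endpoint listed contrasts two of these modes: "Cardiac index at 18 hours (AAI v BiV".
- **Sizing (Statistical Analysis).** The calculation is introduced as paired: "For haemodynamic comparison of paired data at 18 hours to compare BiV pacing to standard (AAI) pacing". Its inputs and result are: "observed a cardiac index of 2.7 ± 0.6", "Allowing a 0.3 L/min/ml^2 ^(11%) improvement in cardiac index", "significance 5% and power 80%, a sample size of 32 subjects would be required".
- **Tests (Statistical Analysis).** A Kolmogorov-Smirnov check is applied to both the primary endpoint and the haemodynamic data. If they pass, the unpaired t-test goes to the former and the paired t-test to the latter. The next sentence gives the only fall-back: "Non-parametric data will be analysed using the Mann-Whitney U or Kruskal-Wallis test".

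No paired or repeated-measures rank test appears anywhere in the article.

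**The concern.** The plan distinguishes paired from unpaired data on the parametric branch and drops the distinction on the non-parametric one. Whether two readings come from the same patient is a matter of design; a normality check has no bearing on it. Mann-Whitney and Kruskal-Wallis would treat the AAI and BiV readings of one patient as if they came from different patients.

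With positively correlated readings, the test then works with too large an error variance. Its p-values are too large, and a real acute haemodynamic benefit, which is the first hypothesis of the trial and has its own sample size calculation, could be missed.

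This is not a detail left to a later analysis plan. The article names the tests, and they do not fit the design that it describes.

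**Working it through.** **1. The plan's own figure.** Inputs from the Statistical Analysis section: SD 0.6, difference 0.3, two-sided 5%, power 80%, (z₀.₉₇₅ + z₀.₈₀)² = 7.85.

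- Paired formula: n = 7.85 × 0.6² / 0.3² = 7.85 × 0.36 / 0.09 = 31.4, rounded up to **32**. The stated figure is reproduced.
- Independent groups: n per group = 2 × 31.4 = 62.8, so **63 per group**. With 32 per group, power would be about 52%.

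The 32 is therefore a paired sample size, and it does not support an independent-sample test.

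**2. The within-patient correlation.** The article gives none. It uses 0.6, the SD of cardiac index in a standard pacing group, as the SD of the paired difference. If each mode also has SD 0.6, then 0.36 = 2 × 0.36 × (1 − ρ), so ρ = 0.5. This is an implied value, not a reported one, so a range is shown.

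**3. Why the test becomes conservative.** An independent-sample comparison takes the variance of the difference as 2σ²/n. With pairing it is 2σ²(1 − ρ)/n. Under the null the test statistic thus has SD √(1 − ρ) instead of 1, and the actual type I error is approximately P(|Z| > 1.96/√(1 − ρ)):

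- ρ = 0.3: 1.96/0.837 = 2.34, giving 1.9%
- ρ = 0.5: 1.96/0.707 = 2.77, giving 0.6%
- ρ = 0.8: 1.96/0.447 = 4.38, giving practically 0%

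**4. Power once the fall-back is in use.** Simulation with 32 pairs, SD 0.6 per mode, difference 0.3, normal margins; 4000 runs per setting (3000 at ρ = 0.8):

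| ρ (assumed) | Wilcoxon signed-rank | Mann-Whitney | Loss (points) | Mann-Whitney type I error |
|---|---|---|---|---|
| 0 | 47% | 48% | none | 4.1% |
| 0.3 | 62% | 48% | about 15 | 2.1% |
| 0.5 | 76% | 48% | 28 | 0.8% |
| 0.8 | 99% | 47% | about 50 | about 0% |

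Log-normal margins give the same pattern: at ρ = 0.5, 73% against 44%, with type I error 0.7%.

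**5. Power of the two-step rule as written.** The fall-back applies only when the normality check rejects. The rule was simulated with the fall-back used if either mode fails the check, and compared with the paired t-test throughout:

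| Data | Kolmogorov-Smirnov version | Check rejects | Power at ρ = 0.5 (rule v paired t) | Power at ρ = 0.8 (rule v paired t) |
|---|---|---|---|---|
| Normal | standard, estimated mean and SD | about 0% | 78% v 78% | no visible loss |
| Normal | Lilliefors-corrected | about 9% | 75% v 78% | 95% v 99% |
| Log-normal, CV 0.6/2.7 = 22% | standard | under 1% | no visible loss | no visible loss |
| Log-normal, CV 22% | Lilliefors-corrected | 24-28% | 72% v 77% | 90% v 99% |

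Allowing for simulation error, the average loss is about 0-6 points at ρ = 0.5 and 0-10 points at ρ = 0.8. Heavier skew would trigger the fall-back more often and raise it.

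**The case against.** The strongest reply is that the large losses describe a procedure the plan would seldom follow. Normal or mildly skewed data mostly pass the check, and the paired t-test, which is appropriate, is then used. This stands: the 28-point loss is conditional on rejection and must not be quoted as the expected loss. The article does not say which version of the Kolmogorov-Smirnov test is meant, and that choice largely decides how often the fall-back is reached.

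It also stands that the correlation is unknown and that the loss vanishes at zero. Zero is hard to believe, however, for readings in one patient taken in the same study session.

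A third reply is that the fall-back sentence was meant only for between-arm data. The text does not support this. The check that leads to it covers the haemodynamic data by name, and Kruskal-Wallis has no role in a two-arm primary comparison. The comparisons described with more than two conditions are the modes, study times and delay settings, all within patients.

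Two stronger readings are tempting. A reader might infer that the haemodynamic analysis will lose much of its power whatever the data look like; step 5 of the working shows otherwise. A reader might also infer from the mismatch that false positive findings are a danger, or that the main result is compromised. With positive correlation the type I error falls below 5%. The primary endpoint, duration of level 3 care, compares two randomised groups, for which Mann-Whitney is suitable.

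**Conclusion.** The sentence is wrong as written: it assigns independent-sample tests to data that the same article defines and sizes as paired. If normality is rejected, power for AAI against BiV at 18 hours falls to about 48%, against about 76% for the matching paired rank test at correlation 0.5. Across normal and mildly skewed data the rule as a whole costs far less, as the working shows.

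These figures rest on 32 pairs, SD 0.6 in each mode, a difference of 0.3, and assumed correlations and data shapes. The harm is limited to a missed effect in one secondary endpoint and the other within-patient comparisons. The primary endpoint and its sample size of 34 are untouched. Severity: minor to moderate.

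**What to change.** Amend the fall-back sentence in Statistical Analysis so that non-normal within-patient comparisons use the Wilcoxon signed-rank test for two modes and the Friedman test for more than two. Keep Mann-Whitney U for comparisons between the randomised arms only. A mixed model with patient as random effect is an option for the several-mode comparisons, but is not needed to correct the error.

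The cost is one sentence of wording, with no new data and no change in sample size. It should be made before the haemodynamic results are analysed, so that the choice of test cannot depend on them.

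### Allocation is minimised on six factors, but the stated between-arm comparison is unadjusted unless baseline looks unmatched, which gives up power if those factors are prognostic

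*Protocol article*

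**What the plan says.** Randomisation (protocol article) assigns two groups with "commercially available software to minimise for confounding variables". Table 6 lists six two-level factors: LV size, QRS duration, Euroscore, intra-aortic balloon pump, valve surgery and ejection fraction.

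Statistical Analysis then fixes the comparison in two data-dependent steps.

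- The primary endpoint and the haemodynamic data are "analysed for normality using the Kolmogorov-Smirnov test". The result sends the data to a t-test or to a rank test, and both are unadjusted.
- Covariates enter only on observed imbalance: "If continuous variables are not matched between intervention and control groups at baseline, inter-group comparisons will be made using an analysis of covariance".

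No stated analysis includes the Table 6 factors as a matter of course. The sample size is for an unadjusted comparison of two means, "with power 80% and with p < 0.05 for a two-sided test", and "the estimated total sample size required is 34 subjects".

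**The concern.** Minimisation makes the arms more alike on the six factors than chance would. The true variance of the treatment difference falls accordingly. An unadjusted test still counts the factors' between-patient variance as error, so its standard error is too large whenever they predict the outcome.

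The imbalance trigger cannot repair this. Minimisation prevents the very imbalance that would fire it. The trigger also speaks only of continuous variables, while balloon pump and valve surgery are yes/no.

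The factors are plausibly prognostic. The article itself treats them as confounders, and in Endpoints a balloon pump with one inotrope counts as level 3 care. At stake is power in a 34-patient trial, and having a single primary p-value settled in advance.

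**Working it through.** **1. The plan's own figure.** Inputs from Statistical Analysis: SD 0.6 days ("reported an average CITU stay of 3.9 ± 0.6 days in the subjects after cardiac surgery"), difference 0.15 × 3.9 = 0.585 days, multiplier 7.85.

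n per arm = 2 × 7.85 × 0.6² / 0.585² = 5.652 / 0.342 = 16.5, rounded up to 17, so 34 in total. The figure reproduces. Power at 17 per arm is 81.1% by the normal approximation and 78.7% by the exact t-test.

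**2. The limiting case.** Let R² be the share of outcome variance explained by the six factors. The article does not give it; 0, 0.2 and 0.4 are assumed. Under perfect balance the difference in means has variance (2/17)σ²(1 − R²), but the unadjusted test uses (2/17)σ². By the normal approximation:

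- Unadjusted type I error = 2 × [1 − Φ(1.96/√(1 − R²))].
 - R² = 0.2: 1.96/0.894 = 2.19, giving 2.8%.
 - R² = 0.4: 1.96/0.775 = 2.53, giving 1.1%.
- Standardised effect = 0.585 / (0.6 × √(2/17)) = 2.84.
- Unadjusted power = Φ((2.84 − 1.96)/√(1 − R²)), which is 84% at 0.2 and 87% at 0.4.
- Adjusted power = Φ(2.84/√(1 − R²) − 1.96), which is 89% and 96%.

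Minimisation falls short of perfect balance and small-sample t critical values apply, so the real figures are less extreme. Simulation is needed.

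**3. Simulation.** 34 patients, six binary factors with assumed prevalences of 0.25-0.5, minimisation with assignment probability 0.8 or 1.0, normal outcome, effect 0.585, SD 0.6. The full-rule columns add five other continuous baseline variables (joint R² 0.1, assumed). There ANCOVA is used if any of the five differs at p < 0.05. Otherwise a Lilliefors-corrected Kolmogorov-Smirnov test chooses between t-test and Mann-Whitney. Ranges span the assignment probabilities and repeat runs; the simulation error is about 0.4 points on type I error and 1 point on power.

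| R² | Type I, unadjusted t | Type I, full rule | Type I, six-factor ANCOVA | Power, unadjusted t | Power, full rule | Power, six-factor ANCOVA |
|---|---|---|---|---|---|---|
| 0 | about 5% | 5.1-5.3% | about 5% | 77-78% | 76% | about 75% |
| 0.2 | 2.7-3.9% | 2.7-3.1% | about 5% | 80-82% | 79% | 84-87% |
| 0.4 | 1.6-2.8% | 1.7-2.1% | about 5% | 81-83% | 80-82% | 91-94% |

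Across repeats, adjustment at R² = 0 costs about 1-4 points of power. A minimisation factor differed between arms at p < 0.05 in only about 1% of runs. In the full rule, chance imbalance in the other variables still triggered ANCOVA in about 21-24% of runs, so the analysis moves without bringing in the factors that matter.

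**4. Skewed durations.** Lognormal outcome (log SD 0.7 and log-scale effect 0.55, both assumed), with the six-factor ANCOVA on the log scale. Power under the full rule is 54-57% against 65-70% adjusted at R² = 0.2, and about 56% against 79-80% at 0.4. Type I error of the rule is 3.7-3.9% and 2.1-2.4%.

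**5. Biomarkers.** Endpoints defines BNP, troponin T and NGAL as change. Assume the same standardised effect, 0.585/0.6 = 0.975, 17 per arm, equal variances at both times, and baseline correlation ρ. The relative variance is 2(1 − ρ) for a change score and 1 − ρ² for ANCOVA. The critical t is about 2.04.

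- ρ = 0.7: 0.975/√(0.60 × 2/17) = 3.67, so power is Φ(1.63) = 95%. For ANCOVA, 0.975/√(0.51 × 2/17) = 3.98, giving 97%.
- ρ = 0.5: 0.975/√(1.00 × 2/17) = 2.84, giving 79%. For ANCOVA, 0.975/√(0.75 × 2/17) = 3.28, giving 89%.

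**The case against.** **What stands against the point.** The R² is unknown, and at 0 the six-factor model is slightly worse. The unadjusted test keeps roughly its planned power throughout, so the design is not broken; efficiency is left unclaimed. A threshold for calling groups unmatched and a list of covariates are details that an unseen analysis plan may supply, and their absence from an article carries no weight here. What the article does state is the rule itself: unadjusted by default, adjusted on observed imbalance.

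**Stronger readings that a reader might infer, and why they fail.**

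- *The rule inflates false positives.* Applied as written it is conservative or on target. An error rate of about 7-10% appeared only when the most favourable result was taken from the t-test, Mann-Whitney and any single-covariate ANCOVA. The article does not permit that choice.
- *The normality test misses skew, so skewed durations go to the t-test.* This depends on the variant, which the article does not name. At 17 per arm and a coefficient of variation of 1.0, the uncorrected test flags about 6-8% of lognormal samples and the Lilliefors-corrected one about 57-60%. Even when the t-test is used, its type I error stayed at 4.2-4.5%. The sound objection is that the choice of test is left to the data.
- *Biomarkers lose a great deal without routine adjustment.* That would hold for raw follow-up values. For markers defined as change, the loss at ρ = 0.7 is about 2 points. Creatinine comes under renal function, which is not stated as change.
- *Centre must also be in the model.* Centre is not a Table 6 factor, and with 34 patients an extra term is not required by this argument.

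**Conclusion.** The concern holds as a loss of efficiency. The analysis does not match the allocation method, and the imbalance trigger will almost never bring the minimisation factors in. With R² assumed, the unadjusted test runs at about 3-4% type I error and about 80% power at 0.2, where adjustment gives 84-87%. At 0.4 it runs at about 2-3% and 81-83%, against 91-94%. At 0 nothing is distorted and adjustment costs about 1-4 points.

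These figures rest on the article's effect and SD, 17 per arm, assumed factor prevalences, equal factor contributions and a normal outcome. The direction is secure; the size is not, because the documents give no R². The change is worth making because the possible gain is well above the possible cost.

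**What to change.** Remove the normality gate and the imbalance trigger. Before any unblinded analysis, pre-specify one primary analysis: ANCOVA of log level 3 duration on arm plus the six Table 6 factors, whatever the observed balance. Report Mann-Whitney as a sensitivity analysis.

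For BNP, troponin T, NGAL and creatinine, always adjust the log value for its log baseline. For the markers analysed as change, the gain is small at a baseline correlation of 0.7 and larger at lower correlations.

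Cost: a change of wording only. The factors are recorded for allocation, the biomarker baselines are already in the Pre-operation schedule, and the total of 34 need not change. The model spends six degrees of freedom in 34 patients, and some levels (balloon pump, ejection fraction ≤ 20%) may be sparse, so the plan should say in advance what happens if a level is empty or nearly so. Trial status reports 31 patients recruited, so the change should be dated and made without sight of outcomes by arm.
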